### Statistical analysis

To assess the gains for each dependent variable (reading, spelling and reading comprehension scores) in each group (1 and 2) and for the total sample, we will calculate the means difference and confidence intervals between T1 and T2 (Phase 1 without training), between T2 and T4 (Phase 2 after 16 weeks of training), between T4 and T5 (Phase 2 after 24 weeks of training), and between T5 and T6 (Phase 3 after 8 weeks without training).The gains between T1 and T2 will be compared with the gains between T2 and T4, between T4 and T5, and between T5 and T6 to determine whether the T2T4, T4T5, and T5T6 differences represent a significantly greater gain compared to the no training phase (T1T2).

To measure the effect of each type of training, we will calculate the effect size, *Cohen’s d* or *η*^*2*^, from the gains of each dependent variable. Cohen’s d scores of 0.3, 0.5 and 0.8 are considered to represent small, medium and large effect sizes, respectively.3.To determine whether the order of PHO/VA versus VA/PHO training leads to different effects, we will perform a repeated Anova with cross-over between groups to compare the gains between T2 and T4 of each group, controlling for gains between T2 and T1 without training. This analysis will also allow us to determine if there is a significant difference between the effects of 8 weeks of phonological training and 8 weeks of visual-attentional training between T2 and T3.4.Exploratory factor analysis will verify that all the items in the questionnaires (pre-test and post-test Likert scale) or, failing that, some of them can be combined into a score. If necessary, the composite scores will be analyzed as continuous variables. If not, graphical representations in the form of histograms will be used to visualize the variations, and χ^**2**^ tests will be carried out.

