## Trial design {8}

The trial is a two-arm crossover multicenter randomized controlled trial conducted in France with 76 speech-language therapists as associate investigators. Randomization will be ensured by means of block randomization with a 1/1 allocation. The framework of this trial corresponds to its overall objective which is to test the superiority of a multimodal and intensive training compared with a non-specific and non-intensive training. Indeed, all children who come to seek dyslexia therapy with a speech and language therapist deserve to be helped and it is ethically difficult to justify that we postpone a potentially effective intervention for 16 months (i.e., children would lose more than an entire year, which is a lot during such a critical developmental phase). For these ethical reasons, we have decided to not to include a no-training control group.

The experiment will take place in three phases over 16 months (see Fig. 2):Phase 1 (baseline): All dyslexic readers participate in one 30-minute session per week with the speech-language therapist for 8 weeks without intensive home training. Reading and spelling exercises are performed as part of the speech and language therapy.Phase 2 (intervention): All dyslexics receive three types of intensive interventions, phonological (PHO), visual-attentional (VA), and cross-modal (CM), that last 2 month each. The order of the first two interventions (PHO and VA) is swapped in two randomly assigned groups of 60 dyslexics each. All children also participate in one 30-minute session per week with the speech-language therapist. For 15 minutes, the speech-language therapist checks that the at-home training instructions are clearly understood. The rest of the session is focused on reading and spelling exercises.

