**Fig. 2 Fig2:**
[figure not shown]
Schematic description of the trial design (see text for details)

CM training takes place at the end of the protocol for two reasons. The first reason is that it might be necessary to first focus on the phonological and visual-attentional processes per se. PHO and VA training should initially improve orthographic and phonological processes and cross-modal training should subsequently re-establish the link between the processing of orthographic representations and the processing of phonological representations. The second reason is that the full randomization of the order of the three types of training would require a much larger sample and more groups. This would increase the risk of not reaching the needed number of inclusions. The number of participants in each group would then be insufficient to obtain sufficient statistical power.

Each training phase lasts for 8 weeks, 15 minutes per day and 5 days per week. Each child benefits from a program adapted to the specific phonological and visual-attentional deficits identified by the cognitive and language profile assessment. For example, children with phonological deficits may receive training to improve phonological awareness and/or phonological short-term memory and/or rapid automatized naming and/or categorical perception (see more explanations p.18). Children with visual-attentional deficits may receive training to improve global-local analysis and/or visual-attentional span. Training will focus on the most impaired deficits. The CM training is the same for all children.Phase 3: All children have one 30-minute session per week with the speech-language therapist over a period of 8 weeks without intensive home training as in Phase 1.

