### Main hypothesis

Intensive and specific multimodal training significantly improves reading (fluency, comprehension) and spelling skills compared to a conventional non-intensive and non-specific therapy. These effects of intervention will be tracked after the three training phases (test 5) and 2 months later (test 6).

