### Eligibility criteria {10}

#### Criteria for inclusion

Age ≥ 8 years old and ≤ 13 years old.Diagnosis of a specific neurodevelopmental reading disorder, according to DSM-5 criteria, with scores ≤ − 1.5 standard deviation from the mean on leximetric tests: Alouette [113, 114], Evaléo 6–15© [115] or Evalec© [116].Phonological deficit: Scores in speed or accuracy lower than 1.5 SD from the mean for phonemic analysis tasks or non-word repetition tasks or automatized quick naming tasks of the Evalec Battery.Visual-attentional deficit: Scores in speed or accuracy lower than 1.5 SD from the average for global or partial reporting tasks of the Evadys© test [117] or for attentional focus tasks of the Sigl© test [118].All children have both at least one phonological deficit and at least one visual-attentional deficit.Family home equipped with a connected computer set up for daily training sessions.Informed consent signed by both parents or by a representative of parental authority.

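### The planned test of training against baseline sets an unscaled 16-week gain against an 8-week gain and forms no T2-T5 contrast, so it does not validly answer the main question; the net direction of bias is unknown

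*Protocol article*

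**What the plan says.** All references are to the protocol article.

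- **Interval lengths.** Trial design {8} describes phase 1 thus: "All dyslexic readers participate in one 30-minute session per week with the speech-language therapist for 8 weeks without intensive home training". Of each of the three training periods it says: "Each training phase lasts for 8 weeks, 15 minutes per day and 5 days per week". Statistical analysis labels the first two trainings "between T2 and T4 (Phase 2 after 16 weeks of training".
- **Planned comparisons.** "The gains between T1 and T2 will be compared with the gains between T2 and T4, between T4 and T5", and also with the T5-T6 gain. The stated aim is to see whether each later gain is significantly greater than the T1-T2 gain. No rate, scaling or time slope is mentioned. The T1-T2 gain serves as an adjustment only in the analysis of training order.
- **Main question.** The Main objective is the combination of the three interventions against baseline. The Main hypothesis adds: "These effects of intervention will be tracked after the three training phases (test 5) and 2 months later (test 6". Main evaluation criteria place reading efficiency at Tests 1, 2, 5 and 6; T3 and T4 appear only under Secondary evaluation criteria.
- **Selection.** Inclusion requires scores at or below -1.5 "standard deviation from the mean on leximetric tests", naming Alouette, Evaléo 6-15 or Evalec. DeltaText is a main reading test that is not named there.
- **Score scale.** Data management {19} allows raw scores, percentiles or standard deviations.
- **Duration.** "The experiment will take place in three phases over 16 months".

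**The concern.** Children aged 8 to 13 who attend school and weekly speech therapy can be expected to make some progress without intensive training. Weekly therapy continues in phase 2, so that progress accumulates over 16 weeks in T2-T4 and over only 8 weeks in T1-T2. If both gains are taken as they stand, a child improving at a constant rate gains twice as much in the longer interval, and the hypothesis tested is false even when training does nothing.

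The comparison also stops at T4, before cross-modal training begins. The contrast that the main objective needs, the whole of phase 2 against phase 1, is not among those listed. Randomisation covers only the order of the first two trainings, and every child passes from phase 1 to phase 2 in the same direction. It therefore cannot correct a mis-specified within-child contrast. At stake is the framework claim of Trial design {8}, to "test the superiority of a multimodal and intensive training compared with a non-specific and non-intensive training".

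**Working it through.** **Intervals, from the article's own figures**

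| Gain | Content | Weeks | Weeks in T1-T2 |
|---|---|---|---|
| T2-T4 | two trainings | 16 | 8 |
| T4-T5 | cross-modal only | 8 | 8 |
| T5-T6 | no intensive training | 8 | 8 |
| T2-T5 (not planned) | all three trainings | 24 | 8 |

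The label attached to T4-T5 in the plan, 24 weeks, is cumulative training time; the interval itself is 8 weeks. The only planned comparison with baseline that covers more than one training is the one of unequal length.

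**Inputs for the size**

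- Completers: 120 × 0.90 = 108 (Sample size {14}).
- Two-sided 5% level, counting rejections in favour of training (nominal 2.5%). The article gives 5%; sidedness is assumed.
- Assumed, because the article gives neither: ordinary progress g, in score SD per 8 weeks, and correlation ρ of 0.8-0.9 between any two occasions.

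**T2-T4 against T1-T2, no training effect**

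- Contrast: (T4-T2) - (T2-T1) = T4 - 2·T2 + T1.
- Null mean: 2g - g = g.
- Variance: (1 + 4 + 1)(1-ρ) = 6(1-ρ), so the SD is 1.10 at ρ = 0.8 and 0.77 at ρ = 0.9.
- One-sample t test, n = 108, no regression to the mean:

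| g | ρ = 0.8 | ρ = 0.9 |
|---|---|---|
| 0.10 | 15% | 26% |
| 0.15 | 29% | 51% |
| 0.20 | 47% | 76% |

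An unscaled T2-T5 comparison would be worse: its null mean is 3g - g = 2g, giving 47-76% already at g = 0.10. Adding T2-T5 without scaling is therefore no repair. With gains put on a common 8-week scale, simulation (5,000 runs, ρ = 0.9, g = 0.1 and 0.2) gave false rejection in favour of training of 1.9-2.2% for T2-T4 and 2.0-2.2% for T2-T5. The equal-length T4-T5 comparison gave 2.2-2.4%.

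**The opposing bias**

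For a test used for selection, with scores below -1.5 SD in a normal population, E[Z | Z < -1.5] = -1.94. Expected regression to the mean by T2 is (1 - reliability) × 1.94:

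- reliability 0.9: 0.1 × 1.94 = 0.19 SD
- reliability 0.8: 0.2 × 1.94 = 0.39 SD

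This raises the T1-T2 gain and is subtracted from the contrast. Setting reliability equal to ρ, the net null mean g - RTM for g = 0.10-0.20 runs from 0.10 - 0.39 = -0.29 to 0.20 - 0.19 = +0.01 SD. False rejection in favour of training is then about 0-3%.

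**A simple threefold contrast**

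(T5-T2) - 3(T2-T1) = T5 - 4·T2 + 3·T1 has a progress term of 3g - 3g = 0 and variance (1 + 16 + 9)(1-ρ) = 26(1-ρ), so the SD is 1.61-2.28. But it carries three times the regression to the mean, -0.58 to -1.16 SD. On a selection test, a training with no effect would then be declared worse than baseline in about 96-100% of trials.

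**Elapsed time**

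8 + 24 + 8 = 40 weeks, about 9 months. Sixteen months is about 70 weeks. Roughly 30 weeks are not assigned to any phase in the text.

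**The case against.** Five points on the other side deserve weight.

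1. **Direction.** A reader might infer that the plan is bound to favour training, with false-positive rates up to 76%. The documents do not support that. Those rates require zero regression to the mean, while selection at -1.5 SD on several of the main tests works in the opposite direction and, on plausible reliabilities, is as large or larger. This stands. It removes any claim about net direction but does not make the test valid, since two opposing biases of unknown size are not a correction.
2. **Labels.** The article calls none of its three comparisons the main one, and two of them are of equal length. This stands, but neither of those two addresses the combined intervention.
3. **Condensation.** The T2-T5 gain is the sum of two gains that will be calculated, and the article may simply be terse. This stands in part. The section nevertheless names its intervals and comparisons explicitly, and the one that matches the main objective is absent.
4. **Score scale.** Age-normed scores could remove part of ordinary progress. This stands, but the article leaves the scale open and includes raw scores and times.
5. **Design disclosure.** A reader might infer that the uncontrolled nature of the comparison is concealed. It is not: the abstract calls phase 1 a within-subject baseline, and Trial design {8} explains why there is no untrained group. Likewise, the 16 months may include breaks shown in Fig. 2 or Table 1, which are not available here. If so, the 2:1 ratio of elapsed time is itself uncertain, which is a further reason to work from actual dates.

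**Conclusion.** The point holds and should be corrected before analysis. Two facts rest on the text alone: the T2-T4 and T1-T2 gains cover 16 and 8 weeks and are compared without scaling, and the T2-T5 contrast required by the main objective, main hypothesis and main evaluation criteria is not formed. Followed as written, the plan tests a null hypothesis that steady progress makes false by one 8-week gain.

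The size is conditional. The 15-26% (0.10 SD per 8 weeks) and 47-76% (0.20 SD) rates depend on assumed progress, an assumed correlation of 0.8-0.9, 108 completers and no regression to the mean. With 0.19-0.39 SD of regression to the mean on tests used for inclusion, the bias may vanish or reverse. The supportable conclusion is that a significant, or a null, T2-T4 result could not be read as evidence on whether the combined training beats usual therapy.

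**What to change.** - Name phase 2 (T2-T5) against phase 1 (T1-T2) as the primary contrast, expressed as the difference in rate of gain per elapsed week.
- Estimate it in a mixed model with piecewise time slopes for the phases, actual test dates, and random effects for child and therapist. The therapist level fits the multi-level intention already stated under Recruitment {15}.
- Do not make (T5-T2) - 3(T2-T1) on the tests used for inclusion the sole primary analysis. Scaling by time repairs the unequal intervals, but regression to the mean stays in the phase 1 slope. Give equal standing to the same rate contrast on DeltaText, where selection on the test's own T1 score does not arise, and report age-normed scores where they exist.
- Reconcile the 16 months with the 40 weeks and define the elapsed time between tests.

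**Cost.** No change to treatment or visits; the work is in the analysis specification. It needs the date of each test, which the case report forms probably hold, although the article does not say so. The rate contrast is noisier: for the same 24-week training effect, the SD rises from √(6(1-ρ)) for the unscaled T2-T5 comparison to √(26(1-ρ)) for the simple threefold form, a factor of √(26/6) ≈ 2.1. Power for the main objective will be less favourable and should be recalculated.

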### Secondary objectives

Assess the efficiency of each intervention against baseline.Assess the efficiency of each intervention as a function of the severity of the “underlying cognitive deficits”.Assess the effects of intensive intervention (phase 2) compared to baseline (phase 1) on reading interest, academic performance, and self-esteem.Assess the stability of the intervention effects in all of the above measures 2 months after training.

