### Secondary hypotheses

*Hypothesis 1*: Intensive phonological or visual-attentional training is more effective than conventional non-intensive and non-specific therapy*Hypothesis 2*: Intensive, specific, multimodal training (test 5) significantly improves reading interest, academic performance, and self-esteem compared to conventional non-intensive therapy (test 2).*Hypothesis 4*: These intervention benefits should last 2 months later (test 6).*Hypothesis 5*: No significant difference as for the effects on reading skills is expected between phonological versus visual-attentional training (test 3).

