### Sample size {14}

In a pilot study on 20 patients with dyslexia, we determined that the effect size on reading efficiency between classical rehabilitation (baseline) and intensive rehabilitation was Cohen d = 0.867. Given that the literature on interventions for children and adolescents with reading disabilities gives effect sizes of 0.322 for phonological interventions (see [34]), expected effects on reading skills of a multimodal phonological, visual-attentional and cross-modal intervention should be greater. However, we preferred to be conservative and reduced the expected effect size to Cohen’s d = 0.700. Using G*Power 3.1.9.6, we found *n* = 55 per group. With an estimated drop-out rate of 10%, we will therefore include 120 participants.

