## Statistical methods

### Statistical methods for primary and secondary outcomes {20a}

The statistical analysis will first include a descriptive analysis of the study population and the parameters studied, globally and by training group, with an assessment of absolute and relative frequencies (and their 95% confidence intervals) for categorical variables, and an assessment of means and standard deviations, medians and interquartiles for quantitative variables. A flowchart will present the number of eligible participants, the number of participants randomized into each group and the number of participants included in the final analysis. The characteristics of participants lost to follow-up during the study will be described. As recommended in the Consort recommendations, participant characteristics will be compared between the two groups at inclusion from a clinical and statistical perspective. Before each analysis is carried out, the conditions of application of the tests used will be verified. The different tests will be considered significant at the 5% threshold (first species risk).

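### The only stated test that uses T6 asks for a greater gain after training stops than before it began, which does not match the aim that benefits last

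*Protocol article*

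**What the plan says.** The Secondary objectives include: "Assess the stability of the intervention effects in all of the above measures 2 months after training". Hypothesis 4 under Secondary hypotheses reads: "These intervention benefits should last 2 months later (test 6"). The Main hypothesis also says that effects will be tracked at test 6, and Test 6 is among the time points of the main evaluation criteria.

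The Statistical analysis section first plans mean differences with confidence intervals for each interval, including "between T5 and T6 (Phase 3 after 8 weeks without training"). It then states the inferential step: "The gains between T1 and T2 will be compared with the gains between T2 and T4, between T4 and T5, and between T5 and T6". The purpose given is to see whether the T2-T4, T4-T5 and "T5T6 differences represent a significantly greater gain compared to the no training phase (T1T2"). One directional rule thus covers two training intervals and one interval without training.

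In the Trial design section (text after Fig. 2), Phase 3 is one weekly 30-minute session "over a period of 8 weeks without intensive home training as in Phase 1". On significance, section 20a says only: "The different tests will be considered significant at the 5% threshold (first species risk").

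**The concern.** Asking for a greater gain than in Phase 1 suits an interval in which training is given. T5-T6 is an interval in which training has stopped. A lasting benefit means that the level reached by T5 is held. It does not require children to improve faster in Phase 3 than in Phase 1 under the same care. A child who keeps everything gained and returns to ordinary progress shows a T5-T6 gain equal to the T1-T2 gain, and the comparison then has nothing to detect.

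Failing to show a greater gain is the expected result under full retention, partial loss and complete loss alike. At stake is the durability conclusion: the one T6 comparison with a stated direction does not address it, and its result is easily misread.

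**Working it through.** **The plan's own figure.** Section 14 states: "we preferred to be conservative and reduced the expected effect size to Cohen’s d = 0.700", with 55 per group and 120 in total. A two-sided two-sample t-test at 5% with d = 0.70 needs 54.02 per group for 95% power, which rounds up to 55. Power is not stated; 95% is the standard value that gives this n. Inflating 110 for 10% drop-out gives 110/0.9 = 122.2, so 123; the stated 120 is close. These figures reproduce and are not affected by this point. Retained children: 120 × 0.9 = 108.

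**Inputs for the T6 comparison.**
- Direction: T5-T6 gain greater than T1-T2 gain (Statistical analysis).
- Both windows: 8 weeks, weekly therapy, no intensive home training (Trial design).
- Threshold 5%, sidedness not stated (section 20a). Two-sided is assumed; one-sided is also shown.

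**Step 1: full retention with ordinary progress.** Let g be the ordinary gain over 8 weeks. Then E(T2-T1) = g and E(T6-T5) = g, so E[(T6-T5)-(T2-T1)] = 0. The chance of a significant result in the stated direction is the upper-tail error rate: 2.5% two-sided, 5% one-sided. This does not depend on n, SD or correlation.

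**Step 2: T6 equals T5 while Phase 1 showed some growth.** The true difference is now negative. With 110 children, a paired t-test and two-sided 5%:

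| Standardised difference | Significantly greater | Significantly smaller |
|---|---|---|
| 0 | 2.5% | 2.5% |
| -0.1 | 0.14% | 18% |
| -0.2 | 0.003% | 55% |

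So a significant result in the opposite direction is not clean evidence of loss either, because it can arise when no child has fallen back.

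**Step 3: what success would need.** For 80% power with 110 children, the T5-T6 gain must exceed the T1-T2 gain by about 0.27 SD of the difference in gains. Progress would have to be faster after training stops than before it began, which no stated hypothesis predicts.

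**Step 4: what a retention analysis can deliver.** Assume equal SDs and one common correlation ρ across T1, T2, T5 and T6; neither is in the article. In units of the score SD, Var[(T6-T5)-(T2-T1)] = 4(1-ρ) per child. With n = 108 and t(107) = 1.98:
- ρ = 0.8: SE = √(0.8/108) = 0.086; half-width 1.98 × 0.086 = 0.17 SD.
- ρ = 0.9: SE = √(0.4/108) = 0.061; half-width 1.98 × 0.061 = 0.12 SD.

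Under full retention, the chance that the lower limit lies above -0.2 SD is about Φ(0.2/SE - 1.98):
- ρ = 0.8: Φ(2.32 - 1.98) = Φ(0.34), about 63%.
- ρ = 0.9: Φ(3.29 - 1.98) = Φ(1.30), about 90%.
- ρ = 0.7: SE = 0.105, Φ(1.90 - 1.98), about 47%.

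A looser margin does better. In simulation (110 children, training effect 0.7 SD, ρ 0.7 to 0.9, full retention), showing that the T5-T6 loss is under half the benefit succeeded in over 99% of trials. Showing that the T2-T6 gain exceeds four times the T1-T2 gain succeeded in about 53-95% when ordinary growth continued in Phase 3. The factor of four is the nominal ratio (24 + 8)/8 weeks.

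**The case against.** A reader might infer that the plan makes this comparison the test of Hypothesis 4, so that 97.5% of trials with a fully maintained benefit would report durability as not shown. The article does not support that. It does not tie the comparison to Hypothesis 4 or to the stability objective, and it nowhere says that a non-significant result means the benefit was lost. The 2.5% is the test's error rate at a true difference of zero, not a forecast of what will be reported.

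A reader might also infer that the planned analysis as a whole cannot tell retention from loss. That too goes too far. The same section plans the T5-T6 mean difference with a confidence interval, by group and for the total sample, and this shows whether scores fell, held or rose. A formal margin may also sit in a fuller document that is not shown.

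The retention contrast has limits of its own. It counts children whose T6 equals T5 as losing ground if T1-T2 showed growth. The article itself raises test-retest effects; if these are larger at T1-T2 than at T5-T6 (an assumption), the contrast is biased towards loss.

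All of this stands and lowers the severity. What it does not answer is that the article leaves nothing open on direction: the only T6 comparison with a stated direction is superiority of gain, and an analysis plan that follows the article would inherit it.

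**Conclusion.** The point holds in limited form and should be fixed. The single inferential comparison that uses T6 tests continued acceleration, while the objective and Hypothesis 4 concern stability. Under full retention with ordinary progress it succeeds at its upper-tail error rate: 2.5% if two-sided, 5% if one-sided. This follows from the direction of the comparison and the identical care in Phases 1 and 3, and rests on no assumed SD or correlation. Its non-significance therefore says nothing about loss.

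The planned T5-T6 interval gives descriptive information, but no maintenance criterion is attached and no T6-versus-T2 comparison is planned. The half-widths of 0.17-0.12 SD and the 63-90% do rest on assumptions: 108 children, equal SDs and a common correlation of 0.8-0.9. The comparisons of the training intervals with T1-T2 do not use T6 and are untouched.

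**What to change.** Remove T5-T6 from the comparison that looks for a significantly greater gain, and state that Hypothesis 4 is assessed by retention:

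1. Report the T5-T6 change with its confidence interval, as already planned.
2. Report (T6-T5)-(T2-T1) with its confidence interval. State which of these two quantities is judged against a loss margin fixed before analysis; benefit is called retained if the lower limit lies above minus that margin. Both windows are nominally 8 weeks, so no rescaling is needed.
3. Report the T2-T6 gain against the gain expected from the phase-1 rate over the same time, using actual elapsed time.
4. State as a limitation that larger retest effects at T1-T2 would bias the contrast in item 2 towards loss.

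The sponsor should choose the margin with its power in view. At 0.2 SD, between about one in ten and more than one in three fully retained cases would miss it for correlations of 0.9 to 0.8. A wider margin is easier to meet but tolerates more loss.

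Cost: a few sentences of analysis wording and one pre-set margin. No new data, visits or participants are needed.

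### The effect size for each type of training is not tied to the excess over the Phase 1 gain, so as naturally read it counts ordinary progress and continuing weekly therapy as training effect

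*Protocol article*

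**What the plan says.** The Statistical analysis section of the protocol article first defines gains as mean differences within a period: T1-T2 (Phase 1), T2-T4, T4-T5 and T5-T6. It then sets the later gains against Phase 1: "The gains between T1 and T2 will be compared with the gains between T2 and T4, between T4 and T5, and between T5 and T6".

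The next paragraph reads "To measure the effect of each type of training, we will calculate the effect size", Cohen's d or eta-squared, "from the gains of each dependent variable", with benchmarks of 0.3, 0.5 and 0.8 for d. It does not mention Phase 1. The order analysis that follows does: "controlling for gains between T2 and T1 without training".

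Elsewhere the contrast is always with baseline:
- Secondary objectives: "Assess the efficiency of each intervention against baseline". The Methods part of the Abstract says the same of each intervention.
- Secondary hypotheses, Hypothesis 1: phonological or visual-attentional training does better than conventional therapy.
- Sample size {14}: the pilot figure is "the effect size on reading efficiency between classical rehabilitation (baseline) and intensive rehabilitation".

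Trial design {8} says of Phase 1: "All dyslexic readers participate in one 30-minute session per week with the speech-language therapist for 8 weeks without intensive home training". The weekly session continues in Phase 2. There is no untrained control group, and both groups receive all three trainings.

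**The concern.** Every child improves to some extent from schooling, growing older, repeated testing and the weekly session. Phase 1 is the design's only way of separating that from what a training adds. If the effect size for a training comes from its own gain alone, the separation is lost at the step meant to say how large the effect is. A training that adds nothing would then show a positive d and could earn a label on the plan's own scale.

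For phonological (PHO) and visual-attentional (VA) training taken singly, nothing else in the section fills the gap. The gains compared with T1-T2 are T2-T4, T4-T5 and T5-T6. T2-T4 pools the two trainings, and no T2-T3 or T3-T4 gain is listed. The T2-T3 analysis compares PHO with VA, not either of them with baseline. The effect-size sentence is therefore the only one in the section that addresses the size of each of these trainings, and it names no comparator.

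**Working it through.** **The plan's own figure.** No effect size for a single training is stated, so there is none to reproduce. The only d with a derived number is in Sample size {14}: d = 0.700 gives 55 per group. An independent two-sample t-test at two-sided 5% gives 55 at 95% power (achieved 0.953), against 34 at 80% and 44 at 90%; the article does not state the power. The figure reproduces. It matters here only because that d derives from a contrast of baseline with intensive therapy.

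**Inputs.** Each training and Phase 1 last 8 weeks (Trial design {8}). The document gives neither a Phase 1 gain nor a between-visit correlation. Assumed: Phase 1 gain g = 0.1, 0.2 or 0.3 score SD per 8 weeks; the same ordinary progress in each later 8-week period; correlation r = 0.7, 0.8 or 0.9; equal score SD at each visit.

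**Formulas.** Let e be what the training adds, in score SD, and S the standardiser.
- Own-gain d = (g + e)/S
- Baseline-referenced d = e/S
- Difference = g/S, whatever the value of e

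S = 1 if the score SD is used. For the SD of gains, S = sqrt(2(1 − r)):
- r = 0.7: sqrt(0.6) = 0.775
- r = 0.8: sqrt(0.4) = 0.632
- r = 0.9: sqrt(0.2) = 0.447

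**Own-gain d over 8 weeks when e = 0 (intended value 0).**

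| Standardiser | g = 0.1 | g = 0.2 | g = 0.3 |
|---|---|---|---|
| Score SD | 0.10 | 0.20 | 0.30 |
| Gain SD, r = 0.7 | 0.13 | 0.26 | 0.39 |
| Gain SD, r = 0.8 | 0.16 | 0.32 | 0.47 |
| Gain SD, r = 0.9 | 0.22 | 0.45 | 0.67 |

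On the plan's benchmarks the top of the score-SD row reaches small, and the top of the r = 0.9 row passes medium. No 8-week value reaches 0.8.

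**When the training does add something.** The shift is the same. With g/S between 0.1 and 0.3, a true excess of 0.322 reads as 0.322 + 0.1 = 0.42 up to 0.322 + 0.3 = 0.62, and one of 0.70 reads as 0.80 to 1.00. With g = 0 the two definitions agree.

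**The case against.** The strongest reply is that the sentence never says the effect size ignores Phase 1. The T1-T2 gain is itself among the gains just defined, the comparisons before and after the sentence use it, eta-squared suits a comparison of gains, and the objectives and the pilot d are all referenced to baseline. A sympathetic reader could take the effect size to be a difference of gains. This stands in part: the document leaves the contrast open and does not fix the wrong one. It does not remove the point, because the authors name the comparator where they want it and omit it here.

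Some stronger statements that a reader might infer are not supported:
- That this effect size is the trial's headline result. The document gives it no such status, and the comparison of gains with T1-T2 already refers to baseline.
- That 0.322 and 0.28 are controlled effects against which an own-gain d would be mismatched. The article calls neither figure controlled.
- That a training adding nothing could be labelled large. That needs the 16-week T2-T4 gain, which spans two trainings and is not the effect of either one.
- That leaving open the standardiser, or the choice between d and eta-squared, is itself an error. Such detail commonly belongs to an analysis plan.

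Two further cautions stand. Data management {19} allows percentiles or standard deviations as well as raw scores, and on age-normed scores ordinary progress need not appear as a gain. Also, children are selected at or below −1.5 SD on leximetric tests, so the SD of their T1 scores may be narrow and would then inflate d. That is a reason not to adopt that SD by default.

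**Conclusion.** The point holds as one of moderate weight. The Statistical analysis section does not tie each training's effect size to the excess over Phase 1. Its natural reading is an uncontrolled pre-post effect, which conflicts with the stated objective and Hypothesis 1. The overstatement equals the standardised Phase 1 gain. Under the assumptions above it is 0.1 to 0.3 on the score SD, or about 0.13 to 0.67 on the gain SD, over 8 weeks. These are illustrations, because the document supplies neither the Phase 1 gain nor the correlation. If the Phase 1 gain is nil, nothing changes. Subtracting that gain removes ordinary progress and retest effects only in so far as they run at the same rate in each period.

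**What to change.** State that the effect size of each training is the mean within-child difference between that training's 8-week gain and the T1-T2 gain, divided by one pre-specified standardiser, with a 95% CI. The 8-week gain is:
- PHO: T2-T3 in the PHO-first group, T3-T4 in the VA-first group.
- VA: T2-T3 in the VA-first group, T3-T4 in the PHO-first group.
- Cross-modal: T4-T5.

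Add the T2-T3 and T3-T4 gains to the list of gains. Put any comparison that uses the 16-week T2-T4 gain on the same 8-week basis as T1-T2. A raw pre-post d may be shown as description only, labelled uncontrolled.

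This needs no new reading data: the five reading tests are already planned at T1 to T5 (Main and Secondary evaluation criteria). The cost is a few sentences, effect sizes that will probably be smaller, and wider intervals. With equal variances and one common correlation r between visits, a single gain has variance 2(1 − r). Gain minus T1-T2 gain has variance 6(1 − r) for T2-T3, which shares T2, and 4(1 − r) for T3-T4 or T4-T5. The SD of the contrast is thus sqrt(3) = 1.73 or sqrt(2) = 1.41 times that of one gain.
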